# Stem cell treatment for regeneration of the rotator cuff: study protocol for a prospective single-center randomized controlled trial (Lipo-cuff)

**DOI:** 10.1186/s13063-024-08557-0

**Published:** 2024-10-19

**Keywords:** Rotator cuff tear, Stem cell treatment, Randomized controlled trial, Oxford shoulder score, Patient-reported outcome

## Abstract

**Background:**

Rotator cuff tears (RCT) are a common musculoskeletal condition, especially in the aging population. The prevalence of rotator cuff tears varies based on factors like age, occupation, and activity level. In the general population, the prevalence of rotator cuff tears is estimated to be around 20 to 25%. Rotator cuff tears (RCT) have an impact in patients’ pain level, shoulder function, sleep disturbance, and quality of life. Primary tendon surgery is in mostly cases necessary. This study aimed to examine if treatment of rotator cuff lesions with implantation of micro-fragmented adipose tissue can improve patients’ reported pain and function compared to conventional surgery.

**Methods:**

The study is a prospective superiority parallel-group single-center randomized controlled trial including 30 patients between 40 and 69 years of age in Denmark. Patients will be allocated 1:1 ratio to reconstruction of the supraspinatus tendon with an injection of micro-fragmented adipose tissue into the related muscle (stem cell treatment) or the standard of care (SOC), which is conventional surgery. Patients, project assistants, physicians, and outcome adjudicators are not blinded to randomization due to practical constraints. The radiologist and the statistician performing the analysis will be blinded. The primary outcome will be the Oxford shoulder score at 12 months post-surgery.

**Discussion:**

This study will assess whether adding micro-fragmented adipose tissue therapy to conventional rotator cuff tear treatment can enhance recovery, accelerate return to daily activities, and improve functional outcomes. The research will also determine if this minimally invasive procedure could be standardized for routine patient care.

**Trial registration:**

ClinicalTrials.gov NCT06505135. Registered on July 10, 2024.

**Supplementary Information:**

The online version contains supplementary material available at 10.1186/s13063-024-08557-0.

## Background

Rotator cuff tear (RCT) is a common shoulder disorder. It is estimated that 65–70% of all shoulder lesions are due to rotator cuff disease [1]. In the general population, the prevalence of rotator cuff tears is estimated to be around 20 to 25% [2]. According to data from the Danish National Patient Register, the incidence rate in 2013 was 715.3 per 10^5^ person-years at risk and the incidence was associated with an increase among people of working age [3]. The tears lead to weakness, pain, and reduced motility in the shoulder [4]. The patients experience markedly reduced quality of life, which also significantly burdens the healthcare system [5, 6], and premature withdrawal from the labor market or exclusion from the workforce is imminent [7]. The cause of rotator cuff tear is multifactorial. Acute trauma, as well as chronic stress, plays a part in combination with inherent factors [8, 9]. Therefore, patient experience is often incorporated into evaluating patient outcomes with a growing focus on standardized assessment and value-based healthcare, and an increased importance of patient-reported outcome measures (PROMs) that assess shoulder status after RCT [10].

Patient-reported outcomes such as Oxford shoulder score (OSS) and quality of life questionnaires are widely used in addition to clinical examination and imaging to assess shoulder status after RCT surgery [11, 12], focusing on value-based healthcare by quantifying a patient’s mental, physical, and functional health, offering a unique perspective to judge the success of surgery [10, 13].

When there is a total rupture of a tendon, surgery often fails to restore optimal function. Initial non-surgical treatment may provide temporary pain relief, but no healing of the lesioned tendon occurs [14]. Several studies indicate that degenerative changes in the damaged tendons and muscles could play a part in the suboptimal results of surgery [15–17].

A recent randomized study tested conventional primary tendon repair and physiotherapy in 103 patients. The authors reported significantly better results for primary tendon repair compared to conservative treatment. Normal function was not regained in any of the conservatively treated patients, and in this group, tear size increased over the years. Besides, patients who crossed to secondary surgery due to failed conservative treatment experienced significantly inferior results compared to primary surgery [18].

Therefore, a strategy that includes primary tendon surgery is meaningful, but with a need for additional treatment that restores the function of the damaged rotator cuff muscle.

Supraspinatus muscle biopsies from 33 patients treated at our hospital and undergoing rotator cuff repair demonstrated the presence of myogenic stem cells. We also found significant variations in stem cell activation, which seemed hampered according to patient age and also the age of the tendon lesion ([name] et al., manuscript submitted for publication, 2023).

Adipose-derived mesenchymal cells are shown to support regeneration in many tissues [19, 20], and animal studies [21], including our own ([name] et al., manuscript in preparation), indicate that injection of cultured adipose cells stimulates myogenesis by activating satellite cells in the torn supraspinatus muscle. The implantation of autologous micro-fragmented adipose tissue could, therefore, be a means for stimulating myogenesis, thereby improving the surgical treatment of rotator cuff lesions.

We hypothesize that combining surgical reconstruction with an injection of micro-fragmented adipose tissue into the supraspinatus muscle will be more effective for treating rotator cuff tears than conventional surgery alone. This approach is expected to result in superior patient-reported outcomes, clinical improvements, which will also be reflected in the radiological results.

The following objectives will be investigated:To investigate if surgery of the shoulder muscle combined with implantation of micro-fragmented adipose tissue can improve function and reduce pain measured by the Oxford shoulder score at 1-year follow-up compared to conventional surgical treatment of rotator cuff lesions.To investigate whether patients experienced improved shoulder function and pain, as measured by the Oxford shoulder score, at 3 and 6 months post-surgery, and enhanced quality of life, as measured by the EQ-5D-5L, at 3, 6, and 12 months post-surgery, following the combination of shoulder muscle repair and micro-fragmented adipose tissue implantation compared to conventional surgical treatment for rotator cuff lesions.To examine if surgery of the shoulder muscle combined with implantation of micro-fragmented adipose tissue can improve clinical and radiological healing of the shoulder at 6 and 12 months compared to conventional surgical treatment of rotator cuff lesions.

## Methods

This protocol followed the recommended reporting guidelines for Standard Protocol Items: Recommendations for Interventional Trials (SPIRIT) [22]. The checklist for SPIRIT is attached as Additional file 1. The study will follow the Consolidation Standard of Reporting Trials (CONSORT) guidelines (parallel-group randomized trials) [23].

### Trial design

The study is a prospective superiority parallel-group single-center randomized controlled trial. The study will recruit patients with rotator cuff tear at the orthopedic outpatient clinic at the Hospital Sønderjylland in Sønderborg, a rural hospital servicing approx. 225.000 inhabitants, and a part of Denmark’s tax-funded healthcare system.

### Population and eligibility criteria

We will include patients between the ages of 40–69 years with clinical signs and symptoms compatible with a traumatic RCT, and who have an MRI verified supraspinatus tear and a reparable lesion with tendon retraction < 2 cm and fatty infiltration level 0–2 according to Fuchs et al. [24] and Goutallier classification [25]. Furthermore, based on the physical status classification system from the American Society of Anesthesiologists (ASA), patients have to be in good health (score < 3) [26].

#### Exclusion criteria

Patients without an MRI of the shoulderFormer surgery in the affected shoulderSigns of infectionImmunosuppression (due to clinical condition or medical therapy)History of inflammatory diseaseMalignancy within 5 yearsPrevious radiotherapy to the shoulderBMI under 18 or above 35CoagulopathyNon-Danish speaking patients

These exclusion and inclusion criteria listed above are identical to those used for the conventional treatment except for the signed consent to the study and language clause (see Fig. 1).

**Fig. 1 Fig1:**
[figure not shown]
Trial population

#### Allocation

Patients will be allocated in a 1:1 ratio to receive either surgical reconstruction of the supraspinatus tendon with an injection of micro-fragmented adipose tissue into the related muscle (stem cell treatment) or the standard of care (SOC), which is conventional surgery.

Allocation will be administered by the project assistant or a physician and generated by a computer using a randomization sequence without stratification with permuting blocks, programmed in a separate document by an independent data manager with no role in the study. The randomization tool in the Research Electronic Data Capture (REDCap) will be used [27]. Patients will be assigned to either the stem cell treatment or SOC at the pre-surgery outpatient examination before their surgery appointment. Allocation concealment is ensured as the project assistant and the physician administering the randomization will be blinded to the randomization code, block sizes, and sequence throughout the trial. Additionally, the randomization is performed electronically and is only revealed after consent is obtained.

#### Blinding

Patients, project assistants, physicians, and outcome adjudicators are not blinded to randomization due to practical constraints. The radiologist and the statistician performing the analysis will be blinded.

### Interventions

After the clinical examination and obtained consent at the outpatient clinic, patients allocated to standard care or intervention groups will be scheduled for a shoulder surgery appointment.

#### Standard of care—rotator cuff surgery

Rotator cuff tendon suture is carried out at Hospital Sønderjylland according to the Danish guidelines for diagnosing and treating patients with shoulder disorders [14]. Standard treatment also includes intravenous injection preoperatively of 2 g of cloxacillin. In case of allergy, 1.5 g of cefuroxime is chosen. Tendon sutures are performed arthroscopically under regional analgetic blockage and light sedation using a standard double-row technique using suture anchors.

#### Stem cell treatment

Patients in the intervention group will receive a stem cell treatment added to the standard care rotator cuff surgery. Assisted by a plastic surgery, an expert in shoulder surgery will conduct all intervention procedures in cooperation with a team specialized in stem cell treatment.

##### Harvest of adipose tissue

Harvest of adipose tissue from abdominal subcutis using the Arthrex ACA Kit® (Arthrex GmbH, Naples, FL, USA), 30 ml of lipoaspirate will be collected from the lower abdomen. After skin preparation, the injection of stromal vascular fraction (SVF) will be performed on an outpatient basis under sterile conditions. In order to obtain the lipoaspirate necessary for the production of SVF, the patient will be injected with tumescent anesthesia and lipoaspirate will be removed from the abdominal fat tissue. Under sterile conditions, an infiltration of 150 ml tumescent solution consisting of 50 ml lidocaine, 1 ml epinephrine, 6 ml sodium hydrogen carbonate, and 1000 ml sodium chloride 0.9% will be performed.

ACP® double syringes. A Carraway Harvester® (Tulip Medical Products (San Diego, CA, USA)) will be connected to the syringes. The Arthrex ACP® double syringe consists of a large and a small syringe which is located in the plunger of the large syringe. The small syringe can be used to remove a liquid fraction that is above a solution after centrifugation without contaminating the remaining or the removed product. In the next step, the lipoaspirate, divided into 15 ml portions per double syringe, will be centrifuged at 2500 rpm in a centrifuge (Rotofix 32A® (Andreas Hettich GmbH & Co. KG, Tuttlingen, Germany) from Hettich Centrifuges) for 4 min at room temperature. The lipoaspirate will be divided into oil, fat graft, and an aqueous fraction. The oil will be transferred to the small syringe and discarded. The aqueous fraction will be removed. The fat graft will be transferred into two 10-ml Luer-Lock syringes and then transferred at least 30 times from one syringe to the other for homogenization using a 1.4-mm connector. Approximately 20 ml of fat graft per collection could be isolated and transferred 30 times from one syringe to the other for further processing.

##### Harvest of muscle biopsy from the supraspinatus muscle

A 0.1–0.2 g muscle biopsy is obtained from the supraspinatus muscle to estimate preoperative muscle fiber atrophy, intracellular lipid accumulation, mitochondrial dysfunction, inflammation, and reduced regenerative capacity. The muscle biopsy specimens will be taken during routine exposure or arthroscopy of the glenohumeral region. Using a blunt shaver, the RC and the musculotendinous junction of the supraspinatus muscle are gently debrided from the fascia and bursal tissue. Biopsies are snap-frozen on dry ice, stored at − 80 °C, or fixed in 10% neutral buffered formalin and embedded in paraffin.

The muscle biopsy will be analyzed with histology, including immunohistochemistry for fiber sizes, inflammation, fibrosis, adipocytes, and myogenesis.

##### Injection of micro-fragmented adipose tissue

In the cell treatment group of patients, injection of the cell suspension will be performed at the end of the surgical procedure. Fluid is carefully aspirated via the anterior outflow cannula, and autologous micro-fragmented adipose tissue is injected in dry arthroscopy conditions from the lateral portal while maintaining a subacromial view from the posterior portal.

Six milliliters of the stem cells suspension will be injected into the supraspinatus muscle at four predefined sites at the musculotendinous junction of the supraspinatus muscle. For each injection site, 1.5 ml of the suspension will be injected using an 18-gauge syringe.

##### In vitro control of the composition of the adipose tissue micro-fraction

The micro-fractions of adipose tissue not used for implantation will be used for control in 2 ways. Part of the material will be used to form a pellet, which can be fixed and embedded in paraffin. Sections of the pellet will be used to characterize the cell composition by immunohistochemistry for the expression of CD45, CD31, CD34, CD146, CD90, ASMA, and S100. These markers have previously been used to characterize adipose-derived cells [28]. Another part of the fractions will be used for explant cultures. In these cultures, the vitality of the cells can be inspected as out-growth from the explants and as proliferation capacity. Moreover, this material can also be used for immunohistochemical characterization of the cell types.

To improve adherence to intervention protocols, the surgical team have a plastic surgeon for the treatment.

#### Relevant concomitant care

All patients will be offered physiotherapy rehabilitation according to Danish clinical guidelines [14].

## Outcomes

### Primary outcome

#### The Oxford shoulder score (OSS) questionnaire

The primary endpoint is the patient-reported shoulder function assessed by the Oxford shoulder score 12 months after surgery reported in mean [11]. The OSS comprises 12 items: four assessing the degree of pain and eight evaluating function. Each item is rated on a 5-point Likert scale, where 0 indicates the worst outcome, and 4 indicates the best. The scores from these 12 items are summed to produce a total score ranging from 0 to 48 [11].

### Secondary outcomes

#### The Oxford shoulder score questionnaire

Improvements in the Oxford shoulder score as above [11] measured 3 and 6 months post-surgery compared to baseline.

#### The EuroQol-5 Dimension (EQ-5D-5L) questionnaire

Median improvements from the baseline in the EQ-5D-5L including self-rated health measured by a visual analog scale (VAS) [29] were assessed at 3, 6, and 12 months, with the 12-month measurement being of primary importance. The EQ5D measures the quality of life on a 5-point Likert scale based on mobility, self-care, usual activities, pain/discomfort, and anxiety/depression, ranging from “no problems” to “extreme problems” [30, 31]. A key feature of the EQ-5D is the availability of “value sets” that weight the health states reported by patients into utility indexes according to the preferences of a country. For the Danish population, these values range from − 0.757 to 1.0, where 1.0 corresponds to absolute health, 0 corresponds to death, and negative values correspond to a health status considered worse than death [32]. The VAS scale is numbered from 0 to 100. 100 means the best health you can imagine. 0 means the worst health you can imagine [29].

#### Clinical healing

Clinical healing will measure pain, function, and strength. (1) Pain will be documented in a range from 0 to 10 and reported in median, (2) pain-free movement (anyhow) above shoulder level reported as yes/no. If the patient is able to have the arm above the shoulder without pain, a (3) strength test will be performed with ISOBEX 4.0, CH3482 Schweiz, and a median for three tests will be recorded in newton. Clinical assessment will be performed at 3, 6, and 12 months in the outpatient clinic and compared between intervention and standard care groups.

#### Functioning of supraspinatus muscle

Improvement of muscle strain in the supraspinatus muscle recorded by speckle tracking ultrasonography (STU) [36]. Muscle strain is a quantitative measure of the contractile properties of muscle tissue [37], and STU patterns will be used to quantify changes in muscle contractility for direct recording of muscle recovery. The maximum voluntary contractions will be reported in newton and the median of five measures of muscle strain of 20%, 40%, and 60% will be documented. The examination will stop if pain is reported. STU will be performed 3, 6, and 12 months after surgery, and changes between the time points will be registered and compared between groups.

### Participant timeline

#### Recruitment

Patients with a confirmed rotator cuff lesion verified by an MRI will have an appointment at the outpatient clinic, where a physician will perform a clinical examination and screening for the study. The responsible surgeon will inform and provide instructions to the physicians performing the first clinical examination and screening of the patients to ensure all patients will be screened. Patients who fulfill the inclusion and exclusion criteria will receive written and oral information about the study provided by the responsible surgeon. As required by ethical rules in Denmark, a quiet atmosphere, a consideration period of a minimum of 24 h, and the possibility of having a companion will be ensured. Consent will be signed by the patient and the surgeon responsible for the study during a subsequent visit. Only patients who give informed consent will be participating in the study. The timeline for the schedule for the participants is presented in Fig. 2.

**Fig. 2 Fig2:**
[figure not shown]
SPIRIT figure with the schematic diagram for the schedule for the participants

### Data collection, management, and analyses

#### Data collection methods

To promote data quality, ensure consistency, reduce the amount of missing data, and increase responsiveness, the project assistant will instruct the study personnel in data collection and reporting. Furthermore, the project assistant will check and supplement for missing data if possible. The patients will fill out the OSS and EQ-5D on their phones in the waiting room at the outpatient clinic, and a study assistant will be present to ensure the successful management of the technology.

All data will be collected through patient interviews regardless of the OSS and EQ-5D questionnaires, which the patients will complete independently.

The demographic data will include patients’ age, gender, social status, occupation, and education. Lifestyle variables comprise smoking history (no, a current smoker, and yes with the amount), alcohol consumption (under or over ten doses), and physical activity (none, under or over 2.5 h). The alcohol consumption report follows the Danish National recommendations [38], and physical activity follows recommendations from the World Health Organization [39]. Clinical data reported will include lesion age in days, how the patient got injured, and sick leave. Pain will be reported on a scale from 0 to 10 at each clinical examination. Medicine information comprises if patients have an intake of statins, any painkillers, or have multipharmacy (> 5 medications). Adverse events will be registered with a date and a description.

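### The 0-10 pain score is taken by interview by unblinded staff, although patients already self-complete two questionnaires on their phones at the same clinic and time points

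*Protocol article*

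**What the plan says.** The Data collection methods section divides the data by mode. For the two questionnaires: "The patients will fill out the OSS and EQ-5D on their phones in the waiting room at the outpatient clinic", with a study assistant at hand to help with the technology. For the rest: "All data will be collected through patient interviews regardless of the OSS and EQ-5D questionnaires, which the patients will complete independently". The same section then places pain with the clinical data: "Pain will be reported on a scale from 0 to 10 at each clinical examination".

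Under Secondary outcomes, Clinical healing, pain is the first of three components: "Pain will be documented in a range from 0 to 10 and reported in median". On timing: "Clinical assessment will be performed at 3, 6, and 12 months in the outpatient clinic and compared between intervention and standard care groups". The Secondary analysis section assigns pain a mixed-effect beta-binomial regression, with a linear mixed model as fallback, so it is formally analysed and is more than a clinical note.

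The Blinding section states: "Patients, project assistants, physicians, and outcome adjudicators are not blinded to randomization due to practical constraints". Only the radiologist and the analysing statistician are blinded. The Monitoring section allows the project assistant to help with clinical assessment when needed.

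**The concern.** A 0-10 pain rating is a patient-reported outcome. Here it is spoken to a member of staff and recorded by someone who, on the text, knows which treatment the patient had. Prompting, interpretation of a vague answer, rounding, or a courteous answer from the patient can each differ by arm. The protocol states a superiority hypothesis and expects better patient-reported and clinical results with the adipose tissue injection, so any such difference could well favour the intervention.

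The two other patient-reported instruments do not take this route. The protocol gives no reason for treating pain differently. The practical constraints it mentions explain why people are unblinded; they do not explain why this item is asked aloud. What is at stake is the credibility of one secondary comparison in a trial with 15 patients per arm.

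**Working it through.** **Step 1. Does the text fix the mode of collection?** Yes. Data collection methods exempts only the OSS and EQ-5D from interview, and lists the 0-10 pain score separately from both, at the clinical examination. Nothing provides for self-completion of this score.

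**Step 2. Would the interviewer know the arm?** The protocol does not name who asks the question. Its list of unblinded people covers project assistants, physicians and outcome adjudicators, and the two blinded roles (radiologist, statistician) do not take pain scores. No blinded interviewer is described.

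**Step 3. Is a self-completion route available at the right times?** The OSS is due at 3, 6 and 12 months (Primary and Secondary outcomes). The EQ-5D measurements "were assessed at 3, 6, and 12 months, with the 12-month measurement being of primary importance". Clinical assessment, including pain, follows the same three time points in the same outpatient clinic. That all three happen at one visit is an inference from this, because the schedule figure is not shown. The order of phone completion and examination is not stated.

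**Step 4. How large could the effect be?** The protocol gives no SD, target difference or power for pain, so there is no figure of its own to reproduce. The following is illustration only.

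Inputs:
- n = 15 per arm (Sample size section).
- Pain SD: assumed 2, range 1.5 to 2.5.
- Interviewer-induced shift b between arms with no true effect: assumed 0.5 or 1.0 point.
- Simple two-sided 5% normal comparison at one time point, without multiplicity adjustment.

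Formulas: SE = SD × √(2/15), and false-positive rate = Φ(b/SE − 1.96) + Φ(−b/SE − 1.96).

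| SD | SE | b = 0.5: b/SE | False-positive rate | b = 1.0: b/SE | False-positive rate |
|---|---|---|---|---|---|
| 1.5 | 0.548 | 0.913 | 0.1475 + 0.0020 = 15.0% | 1.826 | 0.4466 + 0.0001 = 44.7% |
| 2.0 | 0.730 | 0.685 | 0.1011 + 0.0041 = 10.5% | 1.369 | 0.2774 + 0.0004 = 27.8% |
| 2.5 | 0.913 | 0.548 | 0.0789 + 0.0061 = 8.5% | 1.095 | 0.1937 + 0.0011 = 19.5% |

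With b = 0 each row returns 5%. A t-based version with SDs of 2 to 3 gives about 7-10% for a 0.5-point shift and 14-26% for a 1-point shift, so the picture does not depend on the normal approximation.

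**The case against.** The strongest reply is that the fix removes only part of the bias. Patients know their arm, so expectation effects stay in a phone-entered score exactly as they do in the OSS, and a study assistant is present during phone completion. This is correct. The point covers only the additional interviewer component.

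Self-completed pain is also already in the plan: four of the twelve OSS items and one EQ-5D dimension concern pain, and the Secondary analysis section compares arms descriptively across the domains of both instruments. That allows a partial cross-check and lowers the weight of the point. The 0-10 score is still modelled and reported as an outcome of its own.

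The size of the shift has no basis in the document, and the illustration ignores the planned mixed-effect beta-binomial model and the Hochberg procedure. Both criticisms stand, so the percentages show sensitivity and are no estimate of the bias.

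A change after the start of recruitment could mix two modes within 30 patients. This carries little weight for follow-up: recruitment began on September 1, 2024, so no 3-month visit could have taken place before December 1, 2024, after publication on October 19. It does apply to baseline values already taken. Baseline is also the time point least exposed to the problem, since allocation is revealed only after consent, at the pre-surgery outpatient examination, and baseline pain may precede it.

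A reader might infer more than the text supports: that pain is a key secondary outcome, that the treating surgeon takes the score, or that the phone forms are already completed ahead of the examination. The protocol has no key-secondary tier, does not name the interviewer, and gives no order within the visit.

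**Conclusion.** The point holds as an avoidable weakness in how one component of a secondary outcome is collected. The protocol fixes interview as the mode, leaves the relevant staff unblinded, compares and models the score between arms, and has a self-completion route in the same clinic at 3, 6 and 12 months that it does not use for pain. No passages conflict and no figure is miscalculated.

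Its size cannot be determined from the document. If the pain SD lies between 1.5 and 2.5, a 0.5-point shift would give about 9-15% false positives in place of 5% (about 10% at an SD of 2), and a 1-point shift about 19-45%, in a simple unadjusted comparison. It would be tempting to conclude that a small shift is enough to create a false finding. At an SD of 2, a 0.5-point shift still produces none about 90% of the time, so that reading goes too far. Nor does the point threaten the trial's main conclusion, because the OSS is self-completed. The change is worth making because it costs very little.

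**What to change.** Add the 0-10 pain item to the phone form that carries the OSS and EQ-5D. Specify that it is completed before the clinical contact at 3, 6 and 12 months, and also at baseline so that the mode is the same throughout. Name this value as the pain outcome for the between-arm analysis; a rating spoken at the examination can stay in the clinical notes.

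The cost is one extra REDCap item, with no additional visit, staff or change in sample size. The change should be registered and communicated as the Protocol amendments section requires for important modifications. For patients already enrolled, the baseline value taken by interview should be flagged in the data set and the mixed mode mentioned in the report. The report should also say that self-completion does not remove the patients' own expectation bias.
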